#### VR Intervention Procedure

Participants engaged in 1 VR session per day for approximately 20 minutes from their respective ward (orthopedic, vascular, or rehabilitation). At the beginning of the first VR session, after informed consent was obtained and the honorarium was given to the participant, the research assistant administered the sociodemographic and patient characteristic questionnaire (including age, amputation etiology, place of residence, etc). The research assistant then gave a brief verbal introduction to the VR-GMI system and instructed the participant on how to use the VR headset and handheld controls. Following VR instruction and at the beginning of each subsequent VR session, the research assistant verbally administered the Numerical Rating Scales (NRSs; 11-point Likert scales) for PLP, residual limb pain (RLP; ie, physical pain at the amputation site), and nausea before asking if they wanted to engage with the VR program that day. If they declined participation, their reason was recorded.

Participants were only permitted to engage in 1 stage per day. They could only move onto the next VR stage if their RLP, PLP, or nausea NRS scores did not increase by >2 points during or before their next session (given that treatment may exacerbate pain or nausea, and 3 points is considered a clinically significant increase) [44-47]. The participants were permitted to spend as much time as they preferred in each VR stage. If the participant chose to stop the session before the 20-minute goal (a session length used in previous studies) [23,48], the research assistant asked for and recorded their reason for discontinuation. Afterward, the research assistant verbally readministered the NRSs for PLP, RLP, and nausea. Any impromptu feedback or observations made by research personnel were recorded as field notes.

Participants were asked to engage in up to 10 VR-GMI sessions or until hospital discharge, whichever came first. After the last VR-GMI session, before discharge, the Igroup Presence Questionnaire (measuring VR immersion) [49] and VR Impressions Scale (developed by the laboratory for the purposes of descriptive evaluation of a VR intervention; Figure 3) [50] were administered.

**Figure 3 figure3:**
[figure not shown]
The Virtual Reality Impressions Scale.

#### Data Analysis

For the first objective, eligibility and consent rates were calculated according to the number of patients screened. Reasons for refusals or ineligibility were recorded in pie charts. The secondary objective analyzed patient experience with the VR-GMI program by describing the qualitative and quantitative data of each participant individually to capture unique perspectives. Specifically, participant ratings on tolerability (measured by NRS for PLP, RLP, and nausea), immersion (measured by the Igroup Presence Questionnaire), and overall helpfulness (measured by the VR Impressions Scale) were described individually in conjunction with sociodemographic characteristics (such as age, length of hospital stay, etc) to provide context for interpretation. The qualitative data, including participants’ quotes and observations made by research personnel, were integrated to triangulate and increase the strength of the findings.

### Phase 4A: Hospital and Home Feasibility Study (Underway)

#### Overview

In phase 4A, the research team will assess the feasibility and pilot outcomes of the VR-GMI program in the acute postoperative period immediately following LLA (including the hospital and home). The research team aims to recruit 30 participants who recently underwent an LLA through the HSC. A research assistant will visit participants daily to administer the VR-GMI program for approximately 17 days. Participants will then be contacted again 1 month following their final VR session via phone call to assess postoperative PLP. Quantitative data will be collected to assess whether the VR-GMI program and study procedures are sufficient for an RCT.

#### Study Design and Objectives

##### Overview

Phase 4A will consist of a quantitative feasibility study using a 1-group post–test-only design in line with methodological recommendations [33,51]. The feasibility of the program will be evaluated through self-report and administrative quantitative data. The objectives and affiliated hypotheses are mentioned subsequently.

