#### VR Intervention Procedures

Similar procedures to phase 3 will be used in phase 4A, with 3 exceptions made in accordance with preliminary phase 3 data. First, following baseline measure administration, the research assistant will administer a brief video via laptop that introduces the participant to the VR-GMI program, including how to operate the controls and put on the headset. The video (rather than verbal instruction) serves to standardize study expectations and technical knowledge across participants. Second, new measures have been introduced in addition to the measures used in phase 3. The first time a participant completes a stage, they will be administered the Theoretical Framework of Acceptability Questionnaire, which consists of 7 items rated on a 7-point Likert scale inquiring about the acceptability of a behavioral intervention [54] (Figure 4). In addition, following the limb simulation stage (both with and without leg tracking), each participant will be administered the Virtual Embodiment Questionnaire, a validated measure for agency and ownership in a virtual experience involving avatar embodiment [55]. Finally, the Brief Pain Inventory and Patient Reported Outcomes Measurement Information System will be verbally administered over the phone 1 month following each participant’s final VR session to measure PLP intensity and interference, respectively, through validated self-report measures [56-58].

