#### Data Analysis

Objectives 1, 2, and 4 will be evaluated descriptively via bar graphs, means, and SDs to compare each objective across administration settings and VR stage according to preset feasibility criteria. Preset feasibility criteria must be met to determine if the VR program is acceptable (mean Theoretical Framework of Acceptability Questionnaire score >3, which indicates a more favorable acceptability rating than no opinion; Sekhon et al [54]), tolerable (at least 70% of the participants do not report any pre- or post-NRS score increases of ≥3 for PLP, RLP, or nausea), and engaging (mean session duration ≥20 min). Similar progression criteria [52] must be met to determine whether procedural feasibility is appropriate for an RCT, including recruitment (at least 50% of the patients at the HSC who appear to meet the eligibility criteria will be screened through the established pathways), retention (at least 70% of the participants who live in Winnipeg will continue to participate in the study for as long as they are able to), and attrition (at least 80% of the participants will respond at the 1-month follow-up period following their final session) rate criteria. The sample will also be compared to the population of all people who underwent an LLA at the HSC during the recruitment period (from June 2024 to March 2025) via administrative chart review to evaluate whether the characteristics are relatively proportional to one another.

For objective 3, scatterplots will be generated to explore the association between the length of program engagement and the Brief Pain Inventory or Patient Reported Outcomes Measurement Information System pain interference. Mean or median difference in length of program engagement between participants who have and have not yet experienced PLP onset will also be calculated. If appropriate, exploratory regression models will be used to examine the effect of VR dosage on PLP outcomes.

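### Phase 4A collects a daily pre-session PLP rating but names it only for tolerability, so the planned dose–pain plot has no baseline and the design label does not fit

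*Protocol article*

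**What the plan says.** **Design label.** The overview under Phase 4A, Study Design and Objectives, describes a "quantitative feasibility study using a 1-group post–test-only design".

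**Ratings collected.** The Phase 3 VR Intervention Procedure states that, after the initial instruction and then "at the beginning of each subsequent VR session, the research assistant verbally administered the Numerical Rating Scales (NRSs; 11-point Likert scales) for PLP" and for residual limb pain and nausea. This comes before the participant is asked whether to use VR that day. After the session, "Afterward, the research assistant verbally readministered the NRSs for PLP, RLP, and nausea". Phase 4A inherits this: "Similar procedures to phase 3 will be used in phase 4A, with 3 exceptions", and under the second of these "new measures have been introduced in addition to the measures used in phase 3". No phase 3 measure is said to be dropped. On frequency, the Phase 4A overview says: "A research assistant will visit participants daily to administer the VR-GMI program for approximately 17 days".

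**Analyses named.** Phase 4A, Data Analysis, names the rating scale once, in the tolerability criterion: at least 70% of participants with no rise of 3 or more points. For objective 3, "scatterplots will be generated to explore the association between the length of program engagement and the Brief Pain Inventory" or the PROMIS interference score. Both instruments are given once, by phone, 1 month after the last session. The section also plans to compare engagement by PLP onset status and, if appropriate, to fit exploratory regressions of PLP outcomes on VR dose. It does not say which measure feeds either.

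**The concern.** The pilot hypothesis is that participants who spend longer in the program will report lower PLP incidence, intensity and interference. In a single arm, that comparison depends on why some people spend longer. Under the inherited procedure, participants can decline a session or stop it early, and a rise in a pain or nausea rating holds back the next stage. Engagement can therefore depend on pain. If early pain both reduces engagement and predicts pain at 1 month, the planned scatterplot will show the predicted pattern even with no effect of dose. The rating taken before first exposure is the natural baseline for examining this, and no named objective 3 analysis uses it.

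The RCT would also lose useful planning information. The daily series can show how PLP moves in the weeks after amputation, how much it varies between and within people, and how strongly repeated ratings correlate. No named analysis reports any of this.

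**Working it through.** **1. The plan's own sample figure.** Thirty recruited with 5 expected dropouts gives 25/(1 − 5/30) = 30. The figure reproduces and is not in dispute.

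**2. Ratings available.** Seventeen daily sessions give up to 17 pre-session ratings, and 17 × 2 = 34 with the post-session ones. That is up to 25 × 34 = 850 ratings in 25 completers, or 30 × 34 = 1,020 in all 30. The phone call gives one intensity assessment per responder. These are ceilings: participants living outside Winnipeg are discontinued at discharge, so the series length varies with dose.

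**3. Does the label fit?**
- Brief Pain Inventory and PROMIS: only after the last session, so post-test-only is accurate.
- PLP rating: before first exposure, then before and after every session. It is not accurate here, and the tolerability criterion itself uses pre-to-post change.

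**4. What a missing baseline does.** Let *a* be the correlation of early pain with engagement and *b* its correlation with the 1-month score. In a linear model with no dose effect and no other common cause, the expected correlation of engagement with the 1-month score is *a × b*. If pain limits engagement (*a* < 0) and tends to persist (*b* > 0), the product is negative, the direction the hypothesis predicts. The documents give neither value, so the size is unknown.

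**5. Precision of the planned plot.** If the 80% response criterion is only just met, 0.80 × 30 = 24 or 0.80 × 25 = 20 participants have a phone score. For an assumed correlation of magnitude 0.3, Fisher's interval is tanh(atanh 0.3 ± 1.96/√(n − 3)):
- n = 20: −0.16 to 0.66
- n = 24: −0.12 to 0.63

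The plot is imprecise even before confounding is considered.

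**6. Illustration for the mean in-treatment rating only.** With *k* equally correlated ratings, the variance of their mean relative to one rating is (1 + (k − 1)ρ)/k. The documents give no ρ, so it is assumed. At k = 17:

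| ρ (assumed) | Variance ratio | Equivalent independent ratings |
|---|---|---|
| 0.5 | 9.0/17 = 0.53 | 1.9 |
| 0.6 | 10.6/17 = 0.62 | 1.6 |
| 0.7 | 12.2/17 = 0.72 | 1.4 |
| 0.8 | 13.8/17 = 0.81 | 1.2 |

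Seventeen ratings are thus worth about one to two independent ones for a person's average in-treatment pain. The formula assumes no trend over days, and it says nothing about the precision of the 1-month score.

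**The case against.** The strongest reply is that the article does not exclude the daily rating from the PLP analyses. The onset comparison, the conditional regression and the exploratory objective on PLP incidence and intensity leave their source unnamed, and a statistical analysis plan that is not shown could supply it. A reader might infer that the rating serves only the tolerability count and is otherwise discarded. The documents do not support that: its use elsewhere is open, and under the inherited procedure it also governs stage progression. Nor does the pilot outcome rest on one score, since the call has separate intensity and interference instruments and PLP incidence is a further outcome.

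A second tempting inference is that averaging daily ratings would multiply the effective sample or rescue participants who miss the call. It would not. In-treatment pain and pain 1 month later are different quantities. The 80% response figure is a minimum for success, not a forecast of loss.

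Third, a model of pain on accumulated VR minutes has its own problem. Pain affects later dose, and cumulative dose rises with time. In one arm of about 25 completers its coefficient could be mistaken for evidence of efficacy.

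All of this stands and limits the point. What it does not answer is that the article itself fixes the instruments and display for objective 3 intensity, and that display has no baseline although one is collected. It also does not make the label accurate for the repeated ratings.

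**Conclusion.** The point holds in a limited form. The PLP rating is taken before and after each session, its one named phase 4A analysis is tolerability, and the named intensity analysis uses a single phone time point without a baseline. That the rating continues in phase 4A is inferred from the carried-over procedures and confirmed by the pre-to-post tolerability criterion.

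The main consequence is interpretive: the plot cannot distinguish a dose association from early pain limiting engagement. Adjusting for the first rating would reduce this problem without removing it. Loss of precision is a lesser matter and cannot be sized from the documents. No stated figure is wrong and no confirmatory inference is affected. The aim is descriptive and exploratory and the data are collected regardless, so this is an inexpensive improvement to make before the phase 4A analysis.

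**What to change.** 1. Qualify the design label: post-test-only for the phone outcomes, with repeated pre- and post-session ratings of PLP.
2. Name the pre-session PLP rating as a secondary descriptive pilot measure of intensity.
3. Plot each participant's series by days since amputation. Entry is allowed up to 2 months after surgery and the Introduction notes that untreated PLP may improve with time, so session number is a poor time axis.
4. Report between- and within-person SD and correlation for RCT planning, for example from a random-intercept model with days since amputation.
5. In any exploratory regression of the 1-month score on dose, include the first pre-session PLP rating as baseline covariate.
6. Describe any dose coefficient as association only, because pain influences later dose and cumulative dose rises with time.
7. Keep the 1-month score as the later outcome. Use the daily ratings alongside it, not in place of missing 1-month values.

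The cost is a little extra analysis. No new data, visits or participant burden are needed.

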##### Intervention Feasibility

Participants will consider the VR-GMI program to be acceptable, tolerable, and engaging across administration settings (inpatient, outpatient, and home settings) and VR stages.

##### Procedural Feasibility

The used recruitment strategies and study procedures will be appropriate for a RCT, as indicated by comparing sample characteristics to administrative data (reflecting all people undergoing LLAs during the recruitment period) in addition to predetermined recruitment, retention, and attrition rate criteria [52].

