### Future Directions

Beyond this protocol, further development of the VR-GMI program will prioritize clarifying its feasibility and evaluating its efficacy in the postoperative acute period. Depending on the results of phase 4A, additional feasibility studies on the VR-GMI program may be necessary. This may include a longitudinal study conducted in the homes of participants beyond the city limits of Winnipeg to capture a more representative sample. Furthermore, an RCT will be conducted to assess the efficacy of the program. The first RCT will compare virtual GMI to a distractor control (ie, a natural VR environment), while another RCT may compare the program to traditional GMI. The studies enhance the development of an effective VR program to prepare for clinical implementation. Dates for these studies have not yet been determined as initiation depends upon the results of phases 4A and 4B.

The research team also aims to promote visibility of the proposed intervention through brand awareness to spark interest in its use by health care professionals. In line with this aim, the VR-GMI program will henceforth be coined PIVOT (Phantom Pain Graded Motor Imagery Through Virtual Reality Orthopedic Training). PIVOT will be referenced in upcoming publications, which will detail the results of phases 2, 3, and 4. While a name is ultimately a very small change, it is a step toward connecting with health care professionals that may assist with the clinical implementation of PIVOT following prototype development.

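### Phase 4A offers everyone the active program, so its criteria can support RCT suitability only for procedures under open active treatment, not for consent to randomisation or persistence under the control VR

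*Protocol article*

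**What the plan says.** The design is set in the Overview under Study Design and Objectives for phase 4A: "Phase 4A will consist of a quantitative feasibility study using a 1-group post–test-only design". All participants are offered the VR-GMI program, with daily visits for about 17 days, first in hospital and then at home for those living in Winnipeg.

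Three places link this single group to a randomised trial:

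- Phase 4A, Overview: "Quantitative data will be collected to assess whether the VR-GMI program and study procedures are sufficient for an RCT".
- Procedural Feasibility: "The used recruitment strategies and study procedures will be appropriate for a RCT", to be judged by setting the sample against administrative data, together with preset recruitment, retention and attrition criteria.
- Data Analysis: progression criteria "must be met to determine whether procedural feasibility is appropriate for an RCT".

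The recruitment criterion is "at least 50% of the patients at the HSC who appear to meet the eligibility criteria will be screened through the established pathways". Retention requires that at least 70% of participants living in Winnipeg carry on for as long as they can. Attrition requires that at least 80% respond 1 month after their final session.

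Future Directions names the comparator of the first randomised trial: "The first RCT will compare virtual GMI to a distractor control (ie, a natural VR environment".

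**The concern.** A randomised trial against a distractor VR adds to phase 4A that patients must agree to be allocated by chance, and that those allocated to control must keep attending and answer at follow-up without receiving GMI. These steps separate the planned trial from the present study, and phase 4A exercises none of them. If its criteria are met and the article then reports that recruitment and procedures are appropriate for a randomised trial, readers and funders will take the statement to cover steps that were never observed. A problem with acceptance of allocation, or with differential drop-out in the control arm, would first appear in the full trial.

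**Working it through.** No figure in the plan decides this point, so the check sets each element of the go decision against what the planned trial requires.

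| Element in phase 4A | What is counted | Depends on what is offered? | What it tells us about randomisation or control |
|---|---|---|---|
| Recruitment, at least 50% | Apparently eligible patients who are screened | No; it precedes consent | Nothing |
| Retention, at least 70% | Winnipeg residents who continue | Yes; all are on the active program | Nothing about persistence under control |
| Attrition, at least 80% | Responders at 1 month | Yes; all have had the active program | Nothing about response after control |
| Comparison with administrative data | Similarity of the sample to all amputees at the hospital | Partly, through who consents | Representativeness under an open offer only |
| Acceptability, tolerability, engagement | Ratings and session length | Yes; active program only | Nothing about the control VR |

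**Step 1: does any criterion involve consent?** No. The recruitment threshold would be met if half of the apparently eligible patients were screened, however few then agreed, even to the active program.

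**Step 2: does any other part of the plan fill the gap?**

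- Exploratory Outcomes covers reasons for declining, but what is declined is an offer of the active program.
- Results provides for a further feasibility trial if the program needs significant adjustment. A reluctance to be randomised would not trigger this.
- Future Directions makes further feasibility work depend on phase 4A results, which cannot show the gap. Its example is home use outside Winnipeg.
- Strengths and Limitations discusses representativeness and residence outside Winnipeg, not randomisation or control.

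**Step 3: can the size be obtained from the article?** No. The only recruitment count is 15 recruited of 101 screened, 15/101 = 14.9% (exact 95% CI 8.6% to 23.3%). The 101 were screened for eligibility and may include ineligible patients, so this is not a consent rate. It also says nothing about acceptance of a different offer.

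**Step 4: what could a willingness question deliver now?** With a target of 30 and 15 recruited by March 2025, at most 30 − 15 = 15 enrolments remain under the target. If, as an illustration, 80% answered yes:

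- 12 of 15: exact 95% CI 52% to 96%.
- 24 of 30, if participants already enrolled are asked as well: exact 95% CI 61% to 92%.

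This is coarse, but it is more than the present criteria supply.

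**The case against.** The strongest reply is that a single-arm stage before a randomised one is accepted practice. The article places phase 4A at the VR2 stage of its framework and the randomised trial at VR3, in a separate protocol. Any non-randomised feasibility study leaves randomisation untested. This stands, and no control arm is asked for here. It does not justify the wording of the conclusion, which goes beyond the acceptability, feasibility, tolerability and preliminary efficacy that the article gives as the content of VR2.

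It can also be said that Procedural Feasibility is a hypothesis about the strategies and procedures actually used, and that criteria which must be met are necessary rather than sufficient. This has some force for that sentence. It has less for the phase 4A Overview, which speaks of sufficiency, and for Data Analysis, where the criteria determine the answer.

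That the article is condensed does not remove the point, which concerns a conclusion and criteria that it states outright.

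Stronger readings are tempting but not supported:

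- **That the recruitment criterion is inflated by offering active treatment.** It counts patients screened, before any offer is made, so it is not.
- **That the 15 of 101 will set the enrolment assumption for the randomised trial and is too optimistic.** The article reports it only as progress and nowhere uses it to plan that trial.
- **That screening would have to rise by a given percentage.** Any such figure would only restate an assumed refusal rate. The comparator is itself a VR environment, so large refusal is not evident.

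Finally, a willingness question will have limited yield: few approaches remain, and care staff make the first approach, so many who decline never meet research personnel. This is correct and limits what the second part of the fix can show. The first part is unaffected.

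**Conclusion.** The point holds as one about the breadth of the conclusion. None of the three procedural criteria, nor the comparison with administrative data, carries information on consent to randomisation or on persistence and follow-up under the control VR. All can be met while these remain unknown. The article does not show that randomised recruitment would fail or by how much it might fall, and no numerical effect is claimed. The verdict assumes that the first randomised trial uses the comparator named under Future Directions and asks control participants for repeated sessions and follow-up, as phase 4A does; the article does not give that trial's schedule. The correction is worth making because the go decision now reads wider than its evidence and narrowing it costs almost nothing.

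**What to change.** 1. In the phase 4A Overview, Procedural Feasibility and Data Analysis, limit the conclusion to screening, delivery, retention and follow-up procedures under open active treatment. State that acceptability of randomisation and of the control VR remains to be tested. This costs only rewording.

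2. For the remaining approaches, add one yes/no item to the consent and refusal record: would the person take part given an equal chance of receiving the natural VR environment? Where feasible, ask participants already enrolled too, for example at the 1-month call or in the phase 4B focus groups. Report the percentage with an exact 95% CI as a descriptive upper guide, separately for those who enrolled and those who declined, and do not make it a progression criterion.

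Reasons for declining are already recorded. The article also already notes hypothetical willingness to continue among participants living outside Winnipeg, so the item fits existing practice. The cost is a small ethics amendment. The estimate will be imprecise and hypothetical, stated willingness tends to exceed actual willingness, and many people who decline to the care team will be missed.
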